# Interrupting bedtime to reverse frailty levels in acute care: a study protocol for the Breaking Bad Rest randomized controlled trial

**DOI:** 10.1186/s12877-023-04172-x

**Published:** 2023-08-10

**Keywords:** Frailty, Sedentary time, Step counts, Geriatric medicine, ActivPAL, StepWatch

## Abstract

**Background:**

Hospitalized older patients spend most of the waking hours in bed, even if they can walk independently. Excessive bedrest contributes to the development of frailty and worse hospital outcomes. We describe the study protocol for the **Breaking Bad Rest Study**, a randomized clinical trial aimed to promoting more movement in acute care using a novel device-based approach that could mitigate the impact of too much bedrest on frailty.

**Methods:**

Fifty patients in a geriatric unit will be randomized into an intervention or usual care control group. Both groups will be equipped with an activPAL (a measure of posture) and StepWatch (a measure of step counts) to wear throughout their entire hospital stay to capture their physical activity levels and posture. Frailty will be assessed via a multi-item questionnaire assessing health deficits at admission, weekly for the first month, then monthly thereafter, and at 1-month post-discharge. Secondary measures including geriatric assessments, cognitive function, falls, and hospital re-admissions will be assessed. Mixed models for repeated measures will determine whether daily activity differed between groups, changed over the course of their hospital stay, and impacted frailty levels.

**Discussion:**

This randomized clinical trial will add to the evidence base on addressing frailty in older adults in acute care settings through a devices-based movement intervention. The findings of this trial may inform guidelines for limiting time spent sedentary or in bed during a patient’s stay in geriatric units, with the intention of scaling up this study model to other acute care sites if successful.

**Trial Registration:**

The protocol has been registered at clinicaltrials.gov (identifier: NCT03682523).

**Supplementary Information:**

The online version contains supplementary material available at 10.1186/s12877-023-04172-x.

## Background

Frailty is a state of increased vulnerability to adverse health outcomes, due to the accumulation of health deficits [1]. Hospitalized patients living with frailty have a higher risk for functional decline, new impairments in activities of daily living, a longer hospital stay, hospital readmission, and death [2–4]. The risk of hospital-associated deconditioning may be related to the severity of illness, frailty, and hospital structure/processes of care [5]. In general, hospitalized patients spend > 93% of their time lying in bed awake, even if they can walk independently [6]. This excessive sedentary time puts patients’ in-hospital recovery and post-hospital independence at risk. Sedentary time is characterized by a low energy expenditure (< 1.5 metabolic equivalents of task) during awake hours, while in a seated, reclining, or lying posture [7]. Strategies that help address patients’ excessive time spent in bed may attenuate the accelerated development of frailty that accompanies hospital stays.

Based on thigh-worn inclinometry, hospital inpatients are upright for ~ 50 min/day during their waking hours [8], which is much less than reported values of community dwelling older adults (~ 6 h/day; [9]). Observational data have indicated that older patients who walked at least once/day outside their room during hospitalization had ~ 1.7 days shorter length of hospital stay compared with those who stayed in their room [10]. Greater sedentary time in hospitalised older adults is also associated with greater loss of knee-extension strength [11]. While observational studies support the positive impact of moving more on patient health [8, 10], multiple barriers exist to promoting upright time in a hospital, including fall concerns, pain, and lack of patient motivation [12]. Pragmatic interventional studies are needed to help patients move more and limit their sedentary time to address the health impacts of immobility during a hospital stay.

Frailty is a useful outcome measure of overall health state in acute care and is a predictor of adverse health outcomes [13]. However, few interventional studies have measured frailty as an outcome in hospitalized adults [14]. During a randomized clinical trial, two daily sessions of moderate-intensity exercises improved the frailty levels of hospitalized older adults more than the control group [15]. In another study in acute geriatric care, researchers did not observe changes in frailty between the intervention and control groups in those who did, on average, ~five, ~ 20 min sessions of functional exercise sessions over an average of 18 days hospital stay [16]. Perhaps, more frequent patient contact and/or targeting overall physical activity in the absence of periodic structured exercise but combined with goal setting and feedback on performance may be a more feasible approach to helping inpatients move more. The use of goal setting in hospital has been shown to be independently associated with increased physical activity [17]. Our proposed study will strengthen the evidence base of movement and frailty in healthcare by examining whether a step-count based intervention during a patients’ stay in acute care is successful and reduces the level of frailty during hospitalization. Such an understanding is vital to provide guidance on best evidence practice in reducing excessive bed rest in acute care.

The overarching objective of our ***Breaking Bad Rest*** clinical trial is to provide a safe, feasible, and effective intervention that improves the health of inpatients. Using a novel intervention design that involves frequent patient visits, goal setting, and feedback on performance we will determine the feasibility of our ***Breaking Bad Rest*** intervention model in acute geriatric care. We will test the hypothesis that our intervention will improve physical activity and frailty levels and health outcomes to a greater extent than usual care during hospitalization.

## Methods

### Study design and participant selection

The Breaking Bad Rest clinical trial is a randomized controlled trial. The protocol has been registered at clinicaltrials.gov (identifier: NCT03682523) and a SPIRIT checklist is included as Supplemental File 1.

Participants will be approached for this study within 24 h of their admission to the Geriatric Assessment Unit (GAU). The GAU in the QEII Health Sciences Centre in Halifax, Nova Scotia, Canada is a 14-bed acute care inpatient unit that provides interdisciplinary assessment and treatment to older adults with complex medical and social issues.

Our research team will assess patients for eligibility upon admission. The inclusion criteria for this study are: (1) Anticipated hospital stay of more than one day, and (2) Patient or care partner can communicate in English. The exclusion criteria are: (1) Patient or their care partner are not able to provide informed consent, (2) Bedridden prior to hospital admission, (3) Previous participation in our study (i.e., GAU readmission during data collection phase), (4) Near end-of-life or are waiting for long-term care facility placement at GAU admission, or (5) Patient is admitted to a shared room with a current study participant; to avoid risk of behavioural contamination in shared rooms (e.g., additional motivation or demotivation), only one individual in each room will be recruited into the study. We will describe the study to the prospective participant, and/or that person’s care partner and obtain written informed consent. Participants may request to discontinue the study at any point.

No identifying information will be publicly available; patients will be identified only by their study identification numbers. Access to any file relevant to this study will be limited to the study personnel at Nova Scotia Health Authority (NSHA), the NSHA Research Ethics Board (NSHA-REB) and auditors, upon request.

### Sample size

We will recruit 25 participants for the usual care group and 25 participants for the treatment group. This number is based on a previous observational study in which 62% of individuals had an improvement of ≥ 0.10 in their frailty index score during hospitalization (see below for details) [8]. Using these prior estimates, group sample sizes of 25 per group achieves 80% power to detect a relative increase of 50% (i.e., an increase from 62 to 93%) in the proportion achieving a difference of 0.10 in the frailty index. A increase of 0.10 in the frailty index score has been shown to be associated with various adverse health outcomes including extended length of hospital stay, institutionalization, in-hospital falls, delirium, pressure ulcer incidence, and mortality [18].

### Randomization and blinding

Participants will be randomized into intervention or control by a statistician using an n = 6 block design and stratification by participants’ maximum level of mobility at pre-admission. We will identify the patients’ pre-admission mobility level by asking them or their care partner at admission whether the patient, 1) walked independently (i.e., no walking aid or additional person required), 2) required a walking aid (e.g., walker) but not the assistance of another person, or 3) required the assistance of another person. This blocking and stratified randomization was done using the randomizeR package (v2.0.0) [19] and ensures a close to equal number of participants in each group and that the proportion of patients with the same movement capabilities are distributed evenly into the intervention and control groups. The primary investigator and data collection assessors are blinded to participant group assignment; the data analyst will also be blinded.

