### Control group

Those randomized into the control group will receive usual care and will undergo the same social engagement as the intervention group but without the encouragement to engage in more activity and setting activity goals. The control group will receive brief visits from the research assistants conducting the intervention at the same time they went into the unit to visit intervention participants to ensure consistency of the social engagement aspect between intervention-control groups. This entails brief (< 5 min) small talk as how their day is going, if the monitor is annoying them, etc. White boards with random numbers will be placed in the control group patients’ rooms so that the researchers responsible for conducting health assessments will be blind to group allocation.

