## Status to date

The COVID-19 pandemic has delayed the recruitment of participants from our original start date. This was a particular concern given the increased vulnerability of our population of interest. We have attained Research Ethics Board approval from the Nova Scotia Health (ID: 1023828). As outlined in trial registration (NCT03682523), recruitment for this study is on-going.

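### A single published block length of 6 in each mobility stratum would make 20% to 24% of allocations certain in advance to any enroller who knows the stratum's earlier allocations

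*Protocol article*

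**What the plan says.** All references are to the protocol article.

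- **Method of allocation** (Randomization and blinding): the method combines "block design and stratification": participants are "randomized into intervention or control by a statistician using an n = 6 block design", with "stratification by participants’ maximum level of mobility at pre-admission". Mobility has three levels, taken from what the patient or care partner says at admission.
- **Size and ratio** (Sample size): "We will recruit 25 participants for the usual care group and 25 participants for the treatment group".
- **Setting** (Study design and participant selection): the site "is a 14-bed acute care inpatient unit".
- **Who screens** (same section): "Our research team will assess patients for eligibility upon admission". No role is named.
- **Who knows the arms** (Control group): "The control group will receive brief visits from the research assistants conducting the intervention". The same staff therefore see both arms.
- **Who is blinded** (Randomization and blinding): the primary investigator, the data collection assessors and the data analyst.
- **Timing** (Status to date): "recruitment for this study is on-going". The block length became public while allocations were still to be made.

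**The concern.** With a constant block length, the end of a block can be deduced from its beginning. Once three patients in a block of six have gone to one arm, the rest must go to the other. Having a statistician hold the list does not prevent this, because the deduction uses only the block length, which is published, and the earlier allocations, which the delivering assistants know.

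Someone with that knowledge and a hand in entry could influence who is approached, when, or into which stratum. Some room for judgement exists: anticipated length of stay, closeness to end of life, which patient in a shared room is approached, and a mobility level set by a verbal answer. With 25 per arm, a few steered entries could shift the comparison of arms.

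**Working it through.** **Inputs.** Block length 6, three strata and 50 patients at 1:1 come from the article; 3:3 within a block follows from the ratio. I read n = 6 as the block length. Stratum sizes are not given, so every split of 50 into three non-empty strata was examined. The article gives no figure for predictability, so there is none to reproduce.

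**Step 1: certainty within one block.** A 3:3 block has 20 equally likely orderings. An allocation is certain when one arm is already full.

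- Positions 1 to 3: never certain.
- Position 4: certain if the first three are alike, 2/20 = 0.1.
- Position 5: certain if the first four split 3:1, 8/20 = 0.4.
- Position 6: always certain, 1.0.

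The sum is 0.1 + 0.4 + 1.0 = 1.5 per complete block, and 1.5/6 = 25%.

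**Step 2: the whole trial, with unfinished last blocks.**

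- Split 17/17/16: a stratum of 17 is two blocks plus five, 3.0 + 0.5 = 3.5; a stratum of 16 is two blocks plus four, 3.0 + 0.1 = 3.1. Total 3.5 + 3.5 + 3.1 = 10.1, or 20.2% of 50.
- Split 25/18/7: 6.0 + 4.5 + 1.5 = 12.0, or 24.0%.
- Over all splits the range is 20.2% to 24.0%, with a mean of about 21.8%.

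**Step 3: best guesses.** An observer who always names the likelier arm is right with probability 0.5, 0.6, 0.6, 0.7, 0.7 and 1.0 at positions 1 to 6. For 17/17/16 this gives 33.2/50 = 66.4%, against 50% under simple randomization.

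**Step 4: random block lengths of 4, 6 or 8.** These figures are simulated, with an observer who knows the set of lengths and the stratum's history.

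| Scheme (about 17 per stratum) | Certain | Best guess correct |
|---|---|---|
| Fixed 6 | about 20% | about 66% |
| Random 4/6/8 | about 2.5% | about 66% |

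**Step 5: what this means for bias (illustrative).** Suppose an enroller raises prognosis by d SD when expecting one arm and lowers it by d when expecting the other. The bias is then roughly 2d times the net share of correctly steered patients. Take d = 0.5, an assumption with no basis in the article, and the 17/17/16 split.

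- *Steering only on certain allocations.* Fixed 6: 2 × 0.5 × 0.202 = 0.20 SD. Random lengths: 2 × 0.5 × 0.025 = about 0.03 SD.
- *Steering on every best guess.* The net share is 2 × accuracy − 1. Fixed 6: 2 × 0.664 − 1 = 0.328, so about 0.33 SD. Random lengths: 2 × 0.663 − 1 = 0.326, also about 0.33 SD. Simulated type I error of a two-sample t-test is about 18% under both schemes.

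Random lengths therefore help a great deal against someone who acts only when sure, and hardly at all against someone who acts on every guess.

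**The case against.** The strongest reply is that exposure is not shown. The article establishes knowledge of past arms only for the assistants who deliver the intervention. It never says that they screen, obtain consent or enrol. Blinded assessors could do so, and the division of roles may well be set out in the full protocol, which an article need not repeat. This stands, so the point has to be conditional, and silence on who enrols is not itself a fault. What remains is a stated design choice that leaves concealment resting entirely on separation of roles.

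Two further replies also stand. Approach within 24 hours of admission and one participant per room limit discretion over timing. The article also describes the randomization as already carried out, and the number of allocations left is unknown, so the gain may be small.

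A reader might infer more than the article supports:

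- *That random block lengths would bring an inflated type I error back close to 5%.* That contrast appears only if steering is confined to certain allocations, which is the one behaviour the change prevents. Step 5 shows no gain otherwise. The t-test is also not the planned frailty analysis, which uses mixed models and a chi-square test.
- *That no analysis could repair the bias.* Frailty is measured at admission, so imbalance in that measure could be addressed at least in part.
- *That allocation integrity is the only safeguard left.* Assessors and analyst are blinded, and the activity outcomes come from devices.

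**Conclusion.** The point holds as a conditional risk. A fixed block of 6 in each of three strata makes 10 to 12 of 50 allocations (20.2% to 24.0%) certain to a person who knows the block length and every earlier allocation in the stratum. The first condition is met by publication. The second is met by the delivering assistants, but the article does not place them in screening, enrolment or the recording of mobility. It therefore does not support a claim that selection bias is present or that it has any particular size.

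The percentage rests on reading n = 6 as a constant block length with 3:3 allocation. The bias and error figures rest on assumed steering and only illustrate the mechanism. Because the exposure is conditional and the remedy removes certainty but not guessing, this is a change to consider.

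**What to change.** For allocations not yet made:

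1. Give screening, enrolment and the recording of mobility to existing team members who are already blinded to arm, and have the assignment go from the statistician to the delivering assistants without passing through the enroller. This is the more important part.
2. Have the statistician regenerate the rest of each stratum's list with block lengths drawn at random from 4, 6 and 8.
3. Withhold the lengths from everyone who screens, enrols or records mobility.
4. Record the mobility stratum before the allocation is requested.

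**Cost.** A short task for the statistician, a minor amendment, and some rearrangement of duties without new staff. The largest imbalance from an unfinished block rises from 3 to 4 per stratum. If a block open at the switch is cut off, it leaves an imbalance of its own of up to 3; if it is allowed to finish, its last allocations stay predictable. The statistician should choose one course and record it.

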### Intervention group

The intervention group will receive usual care, physical activity monitors (see below for details), and visits from researchers to set daily activity goals and promote movement. Specifically, research assistants (with backgrounds in kinesiology) will visit each patient in the morning and afternoon/evening every day during hospitalization (i.e., 14 times per week) to set a step goal in the morning and check on progress towards this goal later in the day. A white board will be positioned in their room and the specific step goal will be written on it as a target for the patient. A target of up to ~ 20% increase in step counts from the previous day will be initially used. If participants have not achieved their daily goal, feedback will be provided to the patients and patients will be safely mobilized to the maximum level of their ability in the afternoon/evening. While there is a specific step goal, this is not designed to be an all or nothing approach, with the patient encouraged to move to the most of their abilities (e.g., those who are sitting a lot will be encouraged to stand more). Patients who do not meet their target will be encouraged to do whatever is possible within their mobility limits. The research assistants will help facilitate movement and offer going for a brief walk if the patient is interested. The overarching purpose is to promote more movement in an acute care setting to facilitate a more realistic adoption of this intervention into clinical care rather than a pass/fail of specific number of steps increased day-to-day.

### Control group

Those randomized into the control group will receive usual care and will undergo the same social engagement as the intervention group but without the encouragement to engage in more activity and setting activity goals. The control group will receive brief visits from the research assistants conducting the intervention at the same time they went into the unit to visit intervention participants to ensure consistency of the social engagement aspect between intervention-control groups. This entails brief (< 5 min) small talk as how their day is going, if the monitor is annoying them, etc. White boards with random numbers will be placed in the control group patients’ rooms so that the researchers responsible for conducting health assessments will be blind to group allocation.

### Measures

The proportion of patients who finish the study, including the within hospital and post-discharge one-month follow-up phone call will be recorded. The schedule for the measurement of primary and secondary outcomes (described in detail below) are presented in Fig. 1. All data will be input into REDCap, a secure web application for surveys and databases, and initially inspected by a member of the research team not involved with the collection of data. Another separate research assistant not involved in conducting the measures will export the data from REDCap and review it for accuracy prior to statistical analyses.

**Fig. 1 Fig1:**
[figure not shown]
SPIRIT diagram presenting the schedule of enrolment, intervention, and data collection for each research tool over the course of the Breaking Bad Rest trial

### Physical activity and sedentary time

Physical activity and postural positions will be objectively measured continuously (24-hrs per day for all days) throughout the study for both groups. Within 24-hr of admission to the geriatric unit, patients will be outfitted with an activPAL and StepWatch on their thigh and ankle, respectively. The activPAL (activPAL4, PAL Technologies Ltd) is a valid measure of posture [20], distinguishing time spent in upright postures from sedentary/sleeping postures. This monitor will be waterproofed via a nitrile sleeve and attached using Tegaderm medical dressing and replaced every 14 days, if necessary. The StepWatch (Modus Health) will be positioned around the ankle of participants throughout the duration of their hospital visit. This monitor has demonstrated validity in determining step counts, even at slower stepping speeds [21]. The StepWatch has Bluetooth capabilities and will be used to establish patient step goals throughout the study without being taken off and downloaded. Research assistants download step counts in the morning of each day from the StepWatch and use these values to determine the step goals for that day. The primary activity-related outcomes are step counts (via StepWatch), upright time (via activPAL), and total horizontal time (i.e., sedentary and sleep; via activPAL).

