### Frailty index

The frailty index operationalizes frailty in clinical practice and for research [1, 22]. Frailty index scores are calculated as a ratio of health deficits present to total deficits assessed, with a higher value indicating worse frailty levels. For this study, a multi-item frailty index will be calculated based on a health history questionnaire completed by the patient or care partner (if necessary). The specific health questionnaire includes signs/symptoms, mobility, cognition, mood, quality of life, activities of daily living, and nutrition (Supplemental File 2). Frailty will be determined at admission, each week for 1-month (then monthly thereafter), and at a 1-month post-discharge phone call. In hospitalized older adult patients, a change of 0.03 has been demonstrated to be a clinically meaningful change for frailty index scores [23]. In addition to the changes in the continuous frailty score, we will also examine the proportion of patients whose frailty index changes by 0.03 and 0.10 from admission to discharge; 0.10 is considered a moderate change in the frailty index score [24].

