### Statistical analysis

Data collected daily (e.g., physical activity outcomes) or weekly/monthly (e.g., frailty index) will be compared between the intervention and the control group using mixed-models for repeated measures. This modelling accounts for the differences in number of observations between participants, with variability in the number of total days of valid physical activity outcomes. A Chi-Square test of independence will be used to compare the proportion of patients who improve their frailty index scores by ≥ 0.10 or ≥ 0.03 in the intervention and control group at hospital discharge. Measurements conducted at admission and discharge only (e.g., comprehensive geriatric assessment) will be examined via a group by timepoint repeated measures or Friedman’s analysis of variance. Other secondary outcomes (e.g., length of hospital) will be analyzed between the intervention and control groups via independent samples *t*-test and Chi-square tests for continuous and categorical outcomes, respectively.

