## Discussion

The **Breaking Bad Rest** randomized controlled trial aims to promote reducing time in bed and accumulating more step counts during patients’ hospital stay. These findings may provide a novel intervention model for increasing movement in acute care settings and attenuate the development of frailty status among older inpatients. Independent of effectiveness, investigating the feasibility of this type of intervention will be important for the development of future interventions. Specifically, the recruitment of GAU patients that meet our inclusion criteria and conducting a time-intensive intervention protocol to monitor patient activity multiple times each day will be operationally challenging but may inform us if these types of full-time exercise professional positions are warranted. The logistics of timing recruitment within 24-hr of admission to the GAU, conducting weekly assessments in inpatients, and immediately before discharge could be an issue, but the frequent contact of our research team with patients and regular discussions with healthcare providers should mitigate this concern. Importantly, an effort will be put forth to require as little extra work as possible from the GAU staff members (e.g., nurses) to conduct the study, as to test an intervention model that does not add more work responsibilities to the existing staff.

If the study is successful, the model used may be scaled to other acute care units to address the growing concerns of frailty among inpatients.

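### The protocol article names no single primary outcome: the sample size, the frailty section and the label primary point to different ones

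*Protocol article*

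**What the plan says.** All references are to the protocol article.

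- **Background.** The hypothesis is joint: "our intervention will improve physical activity and frailty levels and health outcomes to a greater extent than usual care".
- **Sample size.** The only powered contrast is an increase from 62% to 93% "in the proportion achieving a difference of 0.10 in the frailty index", with 25 patients per group and 80% power. No alpha or sidedness is given.
- **Measures.** The reader is told that primary and secondary outcomes are described in the sections that follow.
- **Physical activity and sedentary time.** "The primary activity-related outcomes are step counts (via StepWatch), upright time (via activPAL), and total horizontal time".
- **Frailty index.** The index is called neither primary nor secondary. Three analyses are listed, the continuous change and two cuts (0.10 and 0.03), with the cuts as additions: "In addition to the changes in the continuous frailty score, we will also examine the proportion of patients whose frailty index changes by". The 0.03 change is described as clinically meaningful and 0.10 as moderate.
- **Secondary outcomes.** The list does not include this questionnaire-based frailty index. It does include another frailty scale, described as a secondary measure of frailty.
- **Statistical analysis.** Daily activity data and the weekly or monthly frailty index "will be compared between the intervention and the control group using mixed-models for repeated measures". For the cuts: "A Chi-Square test of independence will be used to compare the proportion of patients who improve their frailty index scores by" at least 0.10 or at least 0.03. No contrast is singled out.
- **Discussion.** "If the study is successful, the model used may be scaled to other acute care units". Which result would make the study successful is not said.

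**The concern.** A reader who asks which comparison decides this trial gets a different answer from each section. The sample size points to the 0.10 proportion, the frailty section puts the continuous score first, and the explicit label sits on three activity measures.

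These results can disagree. Step counts are what the research assistants coach each day, so they may rise while frailty does not change. One frailty cut may reach significance while the other cut and the continuous score do not. With no primary outcome fixed in advance, whichever result turns out favourable could be presented as the main finding. The 5% error rate and 80% power that justify 25 per group apply only to the 0.10 proportion.

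**Working it through.** **Inputs from the article:** 25 per group; 62% versus 93%; three activity outcomes called primary; three frailty index analyses (continuous, 0.10 cut, 0.03 cut); chi-square for the cuts and mixed models for the rest; monitors worn 24 hours a day.

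**Inputs assumed, because the article does not give them:** two-sided alpha 5% per test; SD of frailty index change 0.08 to 0.15; correlation r between test statistics 0 to 0.8; chi-square with or without continuity correction.

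**Step 1. Reproduce the stated 80%.**

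- Arcsine: h = 2·asin(√0.93) − 2·asin(√0.62) = 0.793. Power = Φ(0.793 × √12.5 − 1.960) = Φ(0.843) = 80.0%.
- Unpooled normal: SE = √(0.62×0.38/25 + 0.93×0.07/25) = 0.1097. Power = Φ(0.31/0.1097 − 1.960) = 80.7%.
- Exact power of the uncorrected chi-square, by enumerating all outcomes: 80.6%.
- Other versions fall short: pooled normal 76.3%, Fisher exact 68.1%, continuity-corrected chi-square 65.0%.

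The stated figure is therefore that of a single two-sided 5% test of the 0.10 proportion, with no alpha spent elsewhere.

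**Step 2. Count the distinct tests.** With 24-hour wear, horizontal time is 24 hours minus upright time, so those two outcomes count as one. Six listed analyses become five distinct ones: three on frailty, plus steps and upright time. If the tests were independent, the chance of at least one p < 0.05 under no effect would be 1 − 0.95⁵ = 22.6% for five, or 1 − 0.95⁶ = 26.5% for six. The tests are not independent, so these are reference values only.

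**Step 3. Illustrate the any-one-wins reading.** I simulated 200,000 null trials at each SD, 25 per arm. Frailty change was normal with 62% improving by at least 0.10. The continuous score was tested by t-test as a stand-in for the mixed model. The two activity statistics were correlated r with each other and with the frailty mean difference.

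| Chi-square | Three frailty tests only | Frailty or activity, r = 0.5 | Frailty or activity, r = 0 to 0.8 |
|---|---|---|---|
| Uncorrected | about 12% | 18–19% | about 15–21% |
| Continuity-corrected | about 7% | about 14% | about 11–16% |

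Over both forms of the test, the range is roughly 11–21%. In the uncorrected case at r = 0.5, about 7% of null trials show a significant activity outcome with all three frailty tests negative.

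Not all of the uncorrected excess is multiplicity. A single uncorrected chi-square at 62% and 25 per arm has an exact size of 5.8%.

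**Step 4. The same trial under other decision rules.** If the 0.10 proportion alone decides, there is no inflation from multiple testing. If both the continuous frailty index and step counts must be significant, the false-success rate is about 0.2–2.1% for r = 0 to 0.8, below nominal.

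**Step 5. Power under two remedies.** With the 0.10 proportion as the single primary, power stays at about 80%. If all six analyses stayed primary with Bonferroni (0.05/6 = 0.0083), power for the 0.10 proportion would be about 57% (arcsine) or 49% (pooled).

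**The case against.** The strongest reply is that the hierarchy is there to be read. The Sample size section powers one contrast, and its figure reproduces. A separate Secondary outcomes section follows the frailty index, which implies that the index ranks above it. In the activity section, primary may mean only primary within the activity domain. These points have force: the label need not be a claim that activity is the trial's overall primary outcome. Even so, they leave three frailty analyses with none named as primary, and the powered one is introduced as the addition.

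A second reply is that this is a condensed article, and that testing order and multiplicity handling belong in an analysis plan that is not shown. That stands, and the absence of an alpha split or a testing sequence is not part of this point. Naming the primary outcome is different. It is protocol content, and the article addresses it in sections that do not agree.

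A third reply concerns the number. A reader might infer that the trial runs a false-positive rate of 18–19%. The documents do not support that as a statement of fact. It needs a rule that any one significant result is a success, which is written nowhere. The hypothesis joins its aims with *and*, which fits a stricter rule equally well. It also needs an assumed alpha, SD and correlation, and an uncorrected chi-square. Finally, the scale-up sentence is a hedged remark in a Discussion that also treats feasibility as an aim, so it is not a decision rule.

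**Conclusion.** The point holds as a conflict between sections. The article powers one frailty contrast, presents it as an additional analysis, and attaches the label primary to three activity outcomes that have no sample size basis. It never says which result decides. This much is on the page and needs no simulation.

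The size is conditional. If any one of the frailty or activity results could be presented as success, the chance of a false success would be roughly 11–21% rather than 5%. That range rests on an assumed two-sided 5% alpha per test, SD 0.08–0.15, correlation 0–0.8 and either form of the chi-square. Under a single deciding contrast, or a rule that requires frailty and activity together, this inflation does not arise. Confidence is high for the conflict and moderate for the range. The change should be made, since it is cheap and settles which of these cases applies.

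**What to change.** - **Sample size, Frailty index and Statistical analysis sections:** name as the single primary outcome the between-group difference in the proportion of patients whose frailty index improves by at least 0.10 from admission to discharge, tested at two-sided 5%. It is the natural choice because the sample size already rests on it.
- **Same sections:** label the continuous frailty index, the 0.03 cut and the activity outcomes as secondary.
- **Physical activity and sedentary time section:** reword the sentence that calls the activity outcomes primary.
- **Claims:** state that any claim of effectiveness rests on the primary outcome.

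Testing order among the secondary outcomes can be left to the analysis plan.

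The cost is wording, plus aligning the registry entry if it differs (the entry was not available here). No extra patients or data are needed, and power stays at about 80%. Recruitment was ongoing at publication and the analyst is to be blinded, so the change can be made before group results are known. The downside is that an isolated significant activity or 0.03-cut result could no longer be presented as trial success.
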